The current study proposes to test whether a 6-week ketogenic diet is an effective treatment for treatment-resistant depression. We will aim to recruit around 100 participants with treatment-resistant depression. On completion of baseline assessments, participants will be randomised 1:1 into the KD group or control group. The KD group involves 6-week pre-prepared ketogenic diet (i.e. the ratio of fat to protein and carbs is 4:1) with weekly KD-focused behavioural and nutritional counselling. The control group will receive weekly nutritional counselling to increase vegetable consumption and reduce saturated fat intake. Participants in the control group will receive food vouchers (£20 every two weeks) to help purchase these items. This aims to be a plausible placebo dietary treatment for depression. Usual treatment for depression will continue, and a leaflet material is provided in both groups (**APPENDIX 9. Dietary materials for the intervention group** and **APPENDIX 10. Dietary materials for the control group**). The primary outcome will be assessed by the difference between groups in the change in self-reported depression severity, using the Patient Health Questionnaire-9 (PHQ-9) (**APPENDIX 8. SELF-REPORTED QUESTIONNAIRES**) at 6 weeks. The secondary outcomes are anxiety score, ability to experience pleasure, work and social adjustment, quality of life, and cognitive performance (**APPENDIX 8. SELF-REPORTED QUESTIONNAIRES**) from baseline to 6 weeks. This trial will also investigate potential mechanistic pathways (i.e. changes in cortisol and gut microbiome) that may explain the effect of a KD on depressive symptoms. We will follow participants to 12 weeks to assess whether they are following the assigned diet and the changes in primary and secondary outcomes.

In this study, a special concern is risk of self-harm and suicide, and further assistance and monitoring are in place. PHQ-9 will be completed every two weeks in the first six weeks and asks participants 'Over the last two weeks, how often have you been bothered by thoughts that you would be better off dead, or of hurting yourself in some way?'

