with response options 'Not at all, several days, more than half the days, nearly every day.' Participants that report that they have had such thoughts more than half the days or nearly every day will have their risk of suicide assessed at the weekly telephone call using the procedure outlined in **Section I. Safety** and Error! Reference source not found.. Anyone judged to have a serious risk of suicide where an emergency response is initiated will be counted as having a serious adverse event.

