**Table 3: Study schedule and follow-up assessments**

| Outcome measures | Baseline assessment (consent to the study) | 2 weeks follow-up assessment | 4 weeks follow-up assessment | 6 weeks follow-up assessment | 12 weeks follow-up assessment |
|------------------|--------------------------------------------|------------------------------|------------------------------|------------------------------|-------------------------------|
| PHQ-9            | ✓                                          | ✓                            | ✓                            | ✓                            | ✓                             |
| GAD-7            | ✓                                          | ✓                            | ✓                            | ✓                            | ✓                             |
| SHAPS            | ✓                                          |                              |                              | ✓                            | ✓                             |
| PDQ-5            | ✓                                          |                              |                              | ✓                            | ✓                             |
| SF-12            | ✓                                          |                              |                              | ✓                            | ✓                             |
| WSAS             | ✓                                          |                              |                              | ✓                            | ✓                             |

|                                                    |   |  |  |   |   |
|----------------------------------------------------|---|--|--|---|---|
| PILT                                               | ✓ |  |  | ✓ | ✓ |
| Substance use and health-related absence from work | ✓ |  |  | ✓ | ✓ |
| Weight                                             | ✓ |  |  | ✓ | ✓ |
| Height                                             | ✓ |  |  |   |   |
| Saliva/Stool samples                               | ✓ |  |  | ✓ |   |
| Interview                                          |   |  |  |   | ✓ |

Note: PHQ-9, Patient Health Questionnaire-9; GAD-7, General Anxiety Disorder Scale; SHAPS, Snaith-Hamilton Pleasure Scale; PDQ-5, Perceived deficits questionnaire-5-item; SF-12, SF Short-Form 12 Health Survey; WSAS, Work and Social Adjustment Scale; PILT, Probabilistic instrumental learning task.

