### 5. Discontinuation/Withdrawal of Participants

If the participant meets any one of the following conditions, the Investigator will stop the treatment at his/her discretion. The participant, however, will not be considered to have dropped out of the study. This may happen for several reasons, including but not limited to:

- a. The participant wishes to stop the treatment.

- b. The Investigator judges that it is difficult to continue the treatment because of emergence of serious adverse events (SAE) as defined below.
- c. The Investigator judges that the risk outweighs benefit in continuing the treatment.
- d. The participant in the KD arm becomes pregnant.
- e. The Investigator judges that it is inappropriate to continue the treatment for other reasons, such as bereavement.

If a participant wishes to withdraw from follow-up, data collected up to the point of withdrawal will still be used, as detailed in the ePIS. The reason for follow-up withdrawal, if provided, will be recorded on the eCRF. No participants will be replaced if they discontinue treatment or withdraw from follow-up.

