##### *Suicide or self-harm risk*

PHQ-9 will be completed every 2 weeks and asks participants 'Over the last two weeks, how often have you been bothered by thoughts that you would be better off dead, or of hurting yourself in some way?' with response options 'Not at all, several days, more than half the days, nearly every day.' Participants that report that they have had such thoughts more than half the days or nearly every day will have their risk of suicide assessed by a telephone call using the procedure outlined in Error! Reference source not found.. If the participant screens positive for "high risk of suicide" a triage guideline will be followed if a positive "high risk" of suicidal intent/plan has been indicated. Participants will be notified that they are not currently eligible for the study at this time, and that further evaluation will be required. We will ring 999 if the participant is in crisis. If there is a significant but not imminent danger, we will inform the GP as outlined in our flow diagram. Regular debriefing and reliability meetings with RAs, psychiatrist consultants, and the lead co-PI will take place to discuss this process. If a participant discloses risk of suicide intent or attempt after baseline and is assessed as not imminently at high risk, the participant will be reminded about the crisis resources by the assessor and resent the link of crisis resources (**APPENDIX 7**).

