### 3. Give details on the medical cover required and who will provide this cover

We have registered medical doctors in the investigating team who are used to assessing patients with psychiatric disorders. Should suicidal ideation be uncovered or other untoward occurrences, the clinicians will respond appropriately, mostly to ensure that usual medical care is provided by the participant's own GP or mental health crisis team. The trial team will ensure that clinical cover is available each day that data is recorded.

A researcher will contact participants the next working day if the response to the PHQ-9 death and suicide question means this is necessary.

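### The protocol gives unreconciled timings for assessing suicide risk after a positive PHQ-9 item 9, and does not say which trial stage its ineligibility sentence covers

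*Combined protocol and SAP*

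**What the plan says.** Protocol Section E treats self-harm and suicide as a special concern. The trigger is a PHQ-9 item 9 answer in either of the two most frequent response categories. Such participants "will have their risk of suicide assessed at the weekly telephone call", and the reader is sent to Section I for the procedure. The same section states that "PHQ-9 will be completed every two weeks in the first six weeks".

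Section I.3 item 2 repeats the trigger. Here participants "will have their risk of suicide assessed by a telephone call using the procedure outlined in" a cross-referenced procedure, with no time given. The paragraph opens with "PHQ-9 will be completed every 2 weeks and asks participants", with no end point. On a high-risk screen it adds: "Participants will be notified that they are not currently eligible for the study at this time".

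Section I.3 item 3 (medical cover) states: "A researcher will contact participants the next working day if the response to the PHQ-9 death and suicide question means this is necessary". Item 5 applies the suicide-risk flow chart in Appendix 7 at baseline and following every PHQ-9.

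Table 3 has a column headed "12 weeks follow-up assessment" in which PHQ-9 is ticked. SAP Table 1 likewise lists PHQ-9 at baseline and weeks 2, 4, 6 and 12.

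On participants whose treatment is stopped, Section G.5 says: "The participant, however, will not be considered to have dropped out of the study". SAP section 3.2 analyses all randomised participants who have at least one measurement of the outcome, in their allocated group.

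**The concern.** Three places describe the response to a worrying item 9 answer, and they differ on when it happens. This is the hazard the protocol itself singles out. A member of staff working from Section E could wait for the next weekly call, while one working from the medical-cover paragraph would make contact the next working day.

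Two smaller problems sit beside this. The weekly-call wording has nothing to attach to at week 12. And the sentence about eligibility appears in the paragraph on repeated PHQ-9 monitoring without saying whether it applies to people already randomised. If staff applied it to them, follow-up could end for reasons related to outcome, contrary to Section G.5 and to the intention-to-treat population.

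**Working it through.** The plan gives no figure to reproduce on this point. The check sets the passages side by side and maps the calls against the PHQ-9 schedule.

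**Step 1, timing.**

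| Place | Action | When |
|---|---|---|
| Section E | Risk assessed | At the weekly call |
| Section I.3 item 2 | Risk assessed | By telephone, no time given |
| Section I.3 item 3 | Researcher makes contact | Next working day, if the answer makes it necessary |

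With calls one week apart, the wait under Section E is between 0 and 7 days. Item 2 sets no limit. Item 3 does not say which answers make contact necessary.

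**Step 2, route.** The weekly calls described are the dietary support calls (Section I.1, SAE definition; Section H). The suicide-risk training in Section I.3 item 2 and the questioning steps in item 5 are written for research assistants. The supplied text therefore leaves open who makes the assessment as well as when.

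**Step 3, calls against PHQ-9 time points.** Treatment lasts 6 weeks (Section H), and SAP section 4.4 counts engagement out of 6 sessions. Taking one call in each of weeks 1 to 6:

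| PHQ-9 at week | Calls in the same or the following week |
|---|---|
| 2 | weeks 2 and 3 |
| 4 | weeks 4 and 5 |
| 6 | week 6 only, the last call |
| 12 | none |

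So the Section E route cannot operate at week 12. Section I.3 item 3 is not tied to weekly calls, and item 5 applies the flow chart after each PHQ-9. Both reach week 12.

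**Step 4, study status.** In Section I.3 item 2, the ineligibility sentence follows directly on the repeated PHQ-9 text, with no stage stated. The only later sentence marked as applying after baseline covers participants judged not to be at imminent high risk. The paragraph therefore does not state the study status of a randomised participant who is at high risk. Section G.5 and SAP section 3.2 both point to continued follow-up and analysis.

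**The case against.** A fair defence of the protocol has four parts.

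First, Section E is background and defers to Section I, and item 3 speaks of contact rather than assessment. The two could be successive steps: contact the next working day, then assessment at the weekly call. That reading is possible, but no passage states it, so the conflict stands.

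Second, week 12. A reader might infer that a positive answer there leads to no contact at all. The documents do not support this, because Section I.3 items 3 and 5 cover it, and Section E introduces its rule with reference to the first six weeks. The open-ended fortnightly wording in item 2 is loose, since Table 3 and SAP Table 1 agree on the schedule. What remains is wording that does not fit one scheduled time point.

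Third, the ineligibility sentence reads like screening text. It matches the suicidal-intent exclusion in Section F.3, the eligibility call in Section F.5 and the screening statement in Section I.4 item 1. That is probably its origin. The objection reduces this part to an ambiguity of stage but does not remove it.

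Fourth, Appendix 7 was not supplied and may settle timing or status. If it does, the body of the protocol should still agree with it.

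**Conclusion.** The timing conflict is firm: next working day in one place, up to about 7 days in another, and unspecified in a third, with no reconciling text in the documents supplied. The 7 days assumes calls one week apart. The week-12 point is a mismatch of wording, not a gap in cover. The eligibility point is an unstated scope, not a planned exclusion.

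A reader might go further and infer that the trial will lose its most severe outcomes and so bias the result. The documents do not support that. No passage withdraws a randomised participant for suicide risk, and suicide risk that prompts an emergency response is counted as a serious adverse event (Sections E and I.1).

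The possible effect can be illustrated only by assumption. With 88/2 = 44 per arm, removing k people who sit 10 points above their arm's mean, from one arm only, lowers that mean by 10k/(44 − k). For k = 2 this is 20/42 = 0.48, and for k = 3 it is 30/41 = 0.73, against a target difference of 5 points. The number removed, the 10-point excess and the one-arm loss are all assumed. Similar losses in both arms would largely cancel, and the mixed model's use of earlier scores would reduce the shift. The sensitivity analyses in SAP section 4.5 would partly expose it. This is a conditional risk, and the importance of the point does not rest on it. It rests on inconsistent instructions about participant safety.

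**What to change.** Reconcile Section E with Section I.3 items 2, 3 and 5 into one statement of timing and route that works at every scheduled PHQ-9, including week 12, and have the other places refer to it. Check Appendix 7 against that statement.

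State which stage the ineligibility sentence covers, and what happens to outcome follow-up for a randomised participant who screens as high risk, consistently with Section G.5 and SAP section 3.2. Which timing and which clinical steps apply is for the investigators to decide.

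SAP section 2.2 records that recruitment stopped at 88 randomised, so new wording can guide only follow-up that is still running. The sponsor should therefore also document which rule staff followed, and report whether any randomised participant was told they were ineligible and whether their outcomes were still collected.

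The cost is a wording amendment, a short briefing for staff still in contact with participants, and a check of the records of the 88 randomised people.

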## Section F. Participants

### 1. Description of research participants

Adults aged 18-65 years with depression, who have been treated with at least two antidepressants in the current episode but still have moderate severity depression ( $\geq 15$ ) as assessed by PHQ-9.

### 2. Inclusion Criteria

- Aged 18-65 years
- Have been diagnosed with depression
- Have had 2 or more antidepressant treatment trials of adequate dose and duration within the current depressive episode to which they did not fully respond. An adequate treatment trial is defined as at least 4 weeks of a medication at a minimum NICE-approved dose
- With a Patient Health Questionnaire-9 (PHQ-9) total score greater than or equal to 15 at baseline
- Able to understand and be willing to adhere to the demands of the study
- Provision of written informed consent
- Have access to a tablet/computer for online assessments, follow-ups with the registered dietitian, and able to attend appointments for assessments and treatment and adhere to study procedures
- Have both a fridge and a freezer at home
- Complete all baseline assessments

### 3. Exclusion criteria

The person may not enter the trial if ANY of the following apply:

- Currently following a low carbohydrate or ketogenic diet
- Currently following a vegan or vegetarian diet as these diets are more challenging to accommodate in a KD and adding vegetables in the control group is unlikely to be seen as helpful.
- Currently receiving, or have received, in-patient psychiatric treatment or electroconvulsive therapy (electric shock to the brain under brief general anaesthetic) within the past year, or scheduled to receive such treatment during the study
- Currently using St John's wort or other remedies for depression that were bought without a doctor's prescription
- Currently have suicidal ideation with intent\* or attempted suicide within the past two months
- Ever had an eating disorder, bipolar disorder, schizophrenia, or psychosis
- Have substance use or alcohol dependence
- Have epilepsy

- Have serious food allergies (experiencing food hypersensitivity that leads to anaphylaxis or other severe symptoms, which may require hospitalisation or are life-threatening) or otherwise require a special diet that cannot be accommodated within a KD such as phenylketonuria or lactose intolerance
- Treated with insulin, sulfonylureas, GLP-1 analogues, or SGLT2 inhibitors
- Women who are pregnant, planning pregnancy in the next three months, or breastfeeding
- Have a body mass index (BMI) of  $<18.5 \text{ kg/m}^2$
- Have unstable or severe medical conditions (e.g., cancer, cardiovascular, renal, lung, psychiatric, or bleeding disorders, diabetes, etc.), currently receiving cancer treatment except hormonal treatment for breast cancer or non-melanoma skin cancer treatment
- Have gallstones, renal tubular acidosis, kidney stones, small bowel malabsorption or a history of pancreatitis
- Have scheduled a major surgery in the next 3 months
- Taking part in other studies that may compromise this study or this study may compromise the other study/ies
- Have read the trial protocol or the clinical trial registration information and therefore are unblinded
- Live in the same household as another participant in the trial
- Not able to complete the online task with a tablet/computer
- Not willing to provide saliva, urine and stool samples

\* We define intent as someone who reports that they have thought of a means of killing themselves and are planning to acquire the means or have acquired them. We will ask participants whether they have ever attempted to end their life in the past in an open question, before narrowing down to assess whether this/these attempts were in the last two months. In the course of this conversation, the history of suicidality will emerge and the RA will keep this as a note, which will help us understand the level of risk.

#### 4. Recruitment

The study will be advertised to the public via: 1) online social media platforms through advertisements created in collaboration with our industrial partner (Native Health Research: <https://www.healthresearch.study/> ) ([Error! Reference source not found.](#)). The social media advertisements will link directly to a Native Health Research landing page (<https://www.healthresearch.study/participate/DIME/> ), where eligible participants will be presented with an electronic participant information sheet (ePIS) ([Error! Reference source not found.](#)); 2) public advertisements placed in pharmacies, community centres, and other community venues. The public advertisements include a printed Native Health Research landing page with a QR code that can be linked to the electronic Native Health Research landing page.

#### 5. Eligibility assessment

Following consent being received, eligibility will be assessed by a two-step consent process.

**Step 1:** Interested people will need to complete an anonymous online screening form to assess eligibility and provide explicit consent to do so but not full consent to enter the study to reduce participant burden. The screening questionnaire assesses the inclusion/exclusion criteria, and is shown in **APPENDIX 3. SCREENING**.

**Step 2:** If potential participants pass the screening questionnaire, participants will be invited to complete the study consent form. Following this, the researcher will conduct a telephone assessment to further evaluate: a) the nature of their usual diet (if applicable); b) the names, duration and doses of antidepressants that they have been taking; c) other medical conditions diagnosed by a doctor; d) the presence of symptoms of psychosis and suicide risk.

The screening for diet, antidepressants and psychosis will comprise asking the following questions and further questions to clarify meaning.

- Q1: “Are you following a specific diet?”
- Q2: if the answer to Q1 is “Yes”, then ask “which diet are you following?”
- Q3: “Can you tell me the names of the antidepressants you’ve been taking, how long you’ve been taking them, and the doses”
- Q4: “Have you had any strange or odd experiences lately that you cannot explain?”
- Q5: “Do you ever hear things that other people cannot hear, such as noises, or the voices of other people whispering or talking?”
- Q6: “Do you ever have visions or see things that other people cannot see?”
- Q7: “Do you ever feel that people are bothering you or trying to harm you?”
- Q8: “Has it ever seemed like people were talking about you or taking special notice of you?”
- Q9: “Are you afraid of anything or anyone?”

If a potential participant responds “No” to questions Q4-Q9, and a response to Q1/Q2 does not indicate a low-carb, ketogenic, vegan or vegetarian diet, they meet the eligibility criteria of not having psychotic symptoms and not currently following an excluded diet. If there is doubt, the RA will pass this to one of the clinical team in the study to assess further. If doubt remains, the person will not be enrolled. If the participant appears eligible, s/he will be invited to complete the baseline assessment and any eligible person who completes this will be enrolled and randomised.

The RA will also ask about suicide ‘risk’ based on the answer to PHQ-9 question 9 to assess whether potential participants can join the study. RA will ask the potential participant if they have been having thoughts that life is not worth living, or that they would be better off dead. If the person’s response indicates that they are experiencing these types of thoughts, the RA will then ask for further details regarding the person’s suicidal thoughts as necessary. This may include questions regarding the frequency and nature of the thoughts and whether specific suicide plans, actions, or attempts have been made. A flow chart has been constructed to demonstrate the appropriate course of action to take in these situations in relation to the person’s responses (Error! Reference source not found.).

The RA will ask participants about the nature of any other illnesses that they have and the treatments they may be receiving, particularly looking for markers that these are having an impact on the participant’s life or rapidly changing or especially severe. If in doubt, this will be passed to one of the medical assessors on the team.

